## Methods/design

### Study aim

The aims of the BePatient trial are to assess the value of eHealth by comparing different levels of telehealth provided to bariatric patients. It is hypothesized that the more eHealth is provided, the higher postoperative weight loss will be, the less likely additional contacts/visits will be consumed, the higher the patients’ satisfaction will be, and the more benefits in co-morbidity will be found. The addition of eHealth provides the patients more self-control, which could result in better commitment to the follow-up program. The primary study hypothesis is that the benefit of adding eHealth to a bariatric care program would lead to a larger reduction in body mass index (BMI) two years after the procedure compared to standard care.

Two main research questions are addressed:Does an eHealth platform increase weight loss after bariatric surgery?Does providing patients with electronical wireless monitoring devices lead to more weight loss?

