### Study setting

This open-label randomized controlled trial is conducted at the Catharina Hospital Eindhoven, a large teaching hospital in the Netherlands. Around 1000 bariatric procedures are performed annually by dedicated bariatric surgeons.

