### Secondary outcome measures

#### Co-morbidity status

Co-morbidity status of diabetes mellitus type 2, hypertension, dyslipidemia, obstructive sleep apnea syndrome, gastro-esophageal reflux disease, and arthralgia is assessed at baseline and at one and two years postoperatively. A co-morbidity is considered in remission if patients do not experience any complaints and if no medication was needed since their last visit. When patients experience fewer complaints or require less medication, the co-morbidity is considered improved. If no changes are seen or when the co-morbidity worsens, it is regarded as unimproved.

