### Statistical analysis

#### Sample size calculation

Lack of standardization for measuring the value of eHealth makes defining relevant endpoints difficult. From a clinical point of view, surgical success is defined as a total weight loss > 20%. The patients not achieving this success could especially benefit from eHealth. Furthermore, there is a group with initial weight loss and subsequent weight regain ending in the same group of failures. In a report from The Longitudinal Assessment of Bariatric Surgery Consortium, which is a multicenter observational cohort study, the results of 2458 patients were reviewed [18]. To evaluate common patterns of weight change from baseline to three years among participants following a gastric bypass, five weight-change trajectory groups were identified. A slight regain of weight occurred in every trajectory group, two years after the procedure different patterns could be distinguished. In another report, trends in weight regain following gastric bypass were reviewed (smaller group, longer follow-up) [19]. Weight gain was found to be a common complication, on average in the range of 21–29% of lost weight. Excessive weight gain was experienced by over one-third of patients. Greater initial absolute weight loss leads to more successful long-term weight outcomes. As the patterns of trajectory groups could be distinguished at two years after the operation with a difference of 10% weight loss, a hypothesis was composed. The difference of 10% corresponds to an arbitrary 4 BMI points. It is, therefore, hypothesized that the addition of eHealth would reduce the BMI by another 4 point at two years postoperatively.

This trial studies the continuous response variable BMI from independent control and experimental participants with two controls per experimental individual. If the true difference in the experimental and control means changes is 4 BMI points with a standard deviation of 8, 48 experimental individuals and 96 controls need to be studied (equal variances assumed) to be able to reject the null hypothesis that the population means of the experimental and control groups are equal with power = 0.8 and α = 0.05. In this trial, two experimental groups are defined. Therefore, at least a total of 200 patients will be enrolled in this trial, assuming no more than 4% missing data.

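### The co-morbidity classes overlap: when complaints and medication move in opposite directions, a patient meets the rule for improved and may also meet the rule for unimproved

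*Protocol article*

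**What the plan says.** The protocol article, under Co-morbidity status, sorts each of six conditions into three classes.

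- Remission: "A co-morbidity is considered in remission if patients do not experience any complaints and if no medication was needed since their last visit". Both components must be satisfied.
- Improved: "When patients experience fewer complaints or require less medication, the co-morbidity is considered improved". Either component suffices.
- Unimproved: "If no changes are seen or when the co-morbidity worsens, it is regarded as unimproved".

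The status of the conditions, which include "gastro-esophageal reflux disease, and arthralgia is assessed at baseline and at one and two years postoperatively", is a named secondary outcome. Under Study aim it carries a directional hypothesis: the more eHealth is provided, "the more benefits in co-morbidity will be found". On blinding, Study setting states: "This open-label randomized controlled trial is conducted at the Catharina Hospital Eindhoven".

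No other section says how to class a patient whose complaints and medication change in opposite directions.

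**The concern.** The rule for improved joins two criteria by an unqualified *or*. A fall in one is enough even if the other has risen. The class meant to hold worsening does not settle such cases, because worsening is not expressed in terms of complaints or medication and is given no priority over improved.

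Two things are at stake. On the literal rule, a patient whose complaints fell because medication was increased counts as a co-morbidity benefit, and so does a patient who takes less medication but has more complaints. If the sentence on worsening is meant to catch these patients, each fits two classes and someone must choose. The trial is open-label and expects more benefit with more eHealth, so that choice is better not left to judgement.

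**Working it through.** **The plan's own figure.** The co-morbidity outcome has no stated rate, effect size or power. The only sample-size figure is for BMI: "4 BMI points with a standard deviation of 8, 48 experimental individuals and 96 controls need to be studied", "with power = 0.8 and α = 0.05". It reproduces. A two-sample t-test with standardised difference 4/8 = 0.5 and two controls per experimental patient needs 47.7 experimental patients, so 48 and 96, with power 0.802. Allowing for 4% missing data, 48/0.96 = 50 and 96/0.96 = 100, and 100 + 50 + 50 = 200. Nothing below changes these numbers.

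**Truth table.** Cross the change in complaints with the change in medication and apply the sentence on improved as written. Remission is left aside: in a patient who had the condition, it lies within the cells where neither component rises.

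| Complaints | Medication | Literal rule for improved | Any component worse? |
|---|---|---|---|
| fewer | less | met | no |
| fewer | same | met | no |
| fewer | more | **met** | **yes** |
| same | less | met | no |
| same | same | not met | no |
| same | more | not met | yes |
| more | less | **met** | **yes** |
| more | same | not met | yes |
| more | more | not met | yes |

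- Meeting improved: 5 of 9 patterns, of which 2 are discordant (bold).
- If worsening means that either component rises, unimproved holds 5 patterns with a rise plus 1 with no change, which is 6. Then 5 + 6 = 11 assignments for 9 patterns, so exactly 2 patterns are classed twice.
- If a fall in one component also requires no rise in the other, 3 of 9 patterns are improved and 6 are not. 3 + 6 = 9, and nothing is classed twice.

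These are counts of patterns, not of patients.

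**Illustration only.** The documents give no rate of discordant change. Suppose a share p of an arm is improved under the stricter rule, and a fraction d of the rest is discordant and scored improved. The observed share is p + (1 − p)d = d + p(1 − d).

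- Equal d in both arms: observed difference = true difference × (1 − d). With an assumed d of 10% to 20%, a true difference shrinks by 10% to 20%.
- Unequal d and no true difference: with an assumed p = 60% in both arms, d = 10% in one arm and 20% to 30% in the other, the spurious difference is 0.40 × (0.20 − 0.10) = 0.04 to 0.40 × (0.30 − 0.10) = 0.08, that is 4 to 8 percentage points. It favours whichever arm is assumed to have more discordance.

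None of these rates comes from the documents. The sign in the second case is simply the assumption put in.

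**The case against.** **The sentence on worsening covers these patients.** Someone with growing complaints on less medication is naturally read as worse, hence unimproved. This stands in part: the documents do not fix that discordant patients are scored as benefit, and a reader who infers that they always are goes beyond the text. But on this reading the patient still satisfies the improved sentence as well, and no order of precedence is given. The fault becomes an overlap; it does not disappear.

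**This is detail for the full protocol.** The article condenses a longer document, and a tie-break for a secondary outcome could sit there. However, the article does state the three class rules, and as stated they conflict. That is more than an omission.

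**There is a device-arm bias.** A reader might infer that home readings prompt treatment changes in the device arm and so inflate its improved rate. The documents do not support this.

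- The Self-monitoring devices section links the synchronised readings to insight into how often the devices are used. The eHealth platform section gives the medical team access to platform data but describes no treatment response.
- The devices are a scale, a blood-pressure meter, an oximeter and an activity tracker. At most they bear on hypertension and perhaps sleep apnoea, two of the six conditions.
- More medication with unchanged complaints does not meet the improved rule at all.
- Patients in other arms may use devices of their own (Inventory of additional support), and every arm has the same standard visits.

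Differential misclassification is possible but not shown.

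**Conclusion.** The point holds as a fault in a stated outcome definition. Two of the five change patterns that meet the literal rule for improved have one component getting worse, and the same two may also meet the rule for unimproved. Depending on the reading, treatment intensification is counted as co-morbidity benefit or the class is left to an open-label assessor.

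This conclusion rests only on the wording of the section and on there being no precedence rule elsewhere in the article. It needs no assumed rate. The size and direction of any bias between arms cannot be computed from the documents, and the 4 to 8 points above should not be quoted as an estimate. The consequence is confined to a secondary outcome with a directional hypothesis. The primary BMI analysis and the sample size are unaffected.

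**What to change.** Make the three classes mutually exclusive, with one sentence in the definition. For example: improved means fewer complaints with no increase in medication, or less medication with no increase in complaints; patients in whom one falls and the other rises are not counted as improved. Use the same reference visit for both components. This is one workable convention. The investigators may choose another, provided it is fixed in advance and every patient falls into one class only.

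Where complaints and medication are recorded separately, also tabulate the two discordant patterns by arm, so that readers can see how common they are and whether the arms differ. The Data collection section names only co-morbidity status among the recorded items, so it should first be checked that the two components are captured.

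The cost is a one-sentence amendment, for which the Study registration section provides a route through the ethics board, and a slightly lower percentage improved. The tabulation costs extra only if the two components are not already held as separate fields.

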#### Quality of life

Health-related quality of life is measured at baseline and at one and two years postoperatively using a Dutch translation of the RAND36 questionnaire [16]. The RAND36 consists of 36 questions derived into nine domains: physical functioning; social functioning; physical role limitations; emotional role limitations; mental health; vitality; pain; general health perception; and health change perception. For each domain, a score of 0–100 is calculated. A low score corresponds with poor health-related quality of life.

#### Return to work

The time it takes for patients to recover until they are fit to work is assessed using a questionnaire six weeks postoperatively.

#### Inventory of additional support

It can be expected that some patients who are randomized in the control or online group will make use of additional support or choose to purchase or use self-monitoring devices themselves. Patients are not limited to seek additional support if they deem that necessary (i.e. mental coaching, sporting activities, Internet forums/groups, other patient platforms, and other self-monitoring devices). To gain insights into this, a yearly questionnaire will be used, which includes questions about the frequency of the use of the abovementioned additional support.

#### Inventory of connections to platform

Information about the data traffic is gathered and stored on the platform. The number of connections is recorded as well as number of page views, time spent per session, and time of the day of the connection. Furthermore, the medium used to access the content (i.e. if the content is accessed on a web browser, mobile phone, or mobile app) is also recorded.

#### Inventory of use of devices

The number and frequency of measurements for each device will be recorded.

#### Satisfaction and commitment questionnaire

Measuring program commitment is assessed yearly with a six-item questionnaire adapted from a version used by Neubert and Cady in 2001 [17]. This includes six yes-or-no questions about their satisfaction and commitment towards the treatment program.

### Data collection

Sociodemographic and clinical information is gathered in the standard follow-up program noted in the patients’ electronic hospital files and is accessible to the treatment team. This includes: sex; age; weight; BMI; status of co-morbidities; quality of life; and blood markers. Additional parameters, such as results of questionnaires, are not normally used in the follow-up program and are therefore stored at a secured part in the Care Coordination Module functionality on the BePatient platform. To analyze the data, individuals are coded in order of registration, starting with 00–001. Members of the research team are responsible for the maintenance and monitoring of completeness and correctness of the data. An annual status report will be sent to the institutional ethical commission.

### Statistical analysis

#### Sample size calculation

Lack of standardization for measuring the value of eHealth makes defining relevant endpoints difficult. From a clinical point of view, surgical success is defined as a total weight loss > 20%. The patients not achieving this success could especially benefit from eHealth. Furthermore, there is a group with initial weight loss and subsequent weight regain ending in the same group of failures. In a report from The Longitudinal Assessment of Bariatric Surgery Consortium, which is a multicenter observational cohort study, the results of 2458 patients were reviewed [18]. To evaluate common patterns of weight change from baseline to three years among participants following a gastric bypass, five weight-change trajectory groups were identified. A slight regain of weight occurred in every trajectory group, two years after the procedure different patterns could be distinguished. In another report, trends in weight regain following gastric bypass were reviewed (smaller group, longer follow-up) [19]. Weight gain was found to be a common complication, on average in the range of 21–29% of lost weight. Excessive weight gain was experienced by over one-third of patients. Greater initial absolute weight loss leads to more successful long-term weight outcomes. As the patterns of trajectory groups could be distinguished at two years after the operation with a difference of 10% weight loss, a hypothesis was composed. The difference of 10% corresponds to an arbitrary 4 BMI points. It is, therefore, hypothesized that the addition of eHealth would reduce the BMI by another 4 point at two years postoperatively.

This trial studies the continuous response variable BMI from independent control and experimental participants with two controls per experimental individual. If the true difference in the experimental and control means changes is 4 BMI points with a standard deviation of 8, 48 experimental individuals and 96 controls need to be studied (equal variances assumed) to be able to reject the null hypothesis that the population means of the experimental and control groups are equal with power = 0.8 and α = 0.05. In this trial, two experimental groups are defined. Therefore, at least a total of 200 patients will be enrolled in this trial, assuming no more than 4% missing data.

#### Data analysis

Descriptive statistics of the data will be performed for all baseline characteristics and outcome measures. Groups will be compared using ANOVA-tests and χ^2^-tests (normal distribution) or Mann–Whitney *U*-tests (non-normal distribution) to analyze outcome measures. Comparisons of baseline characteristics will be done descriptively. Due to the repeated measure nature of the design (preoperative, one year postoperatively, and two years postoperatively) repeated measure ANOVA will be used to analyze weight-loss patterns between the intervention groups and over time.

SPSS v.25.0 (IBM Corp., Armonk, NY, USA) is used for statistical analysis and handling of data. Analysis will be performed using the intention-to-treat principle. A *p* value < 0.05 (two-sided) will be considered statistically significant. Subgroup analysis may help identify subgroups in which interventions work better or worse. Therefore, predetermined subgroup analysis will be performed. A subgroup analysis will be done comparing active platform or device users with inactive users to determine if activity influences outcome. Also, several age groups will be analyzed, as older patients might have a harder time working with electronical device and the online platform. Finally, a subgroup analysis will be performed comparing gender.

Substantial amounts of missing data will be handled using multiple imputations if deemed necessary.

Outcomes are planned to be published in a peer-reviewed journal upon completion of this trial.

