### Randomization and treatment allocation

Participants who fulfill all selection criteria and signed the informed consent form are randomized in a 2:1:1 ratio. Simple randomization is used, meaning every individual has an equal chance to be enrolled in one of the three groups. Allocation is into one of three groups: (1) control group (*n* = 100); (2) platform group (*n* = 50); and (3) device group (*n* = 50). This randomization is computer-generated in a Care Coordination Module functionality in the BePatient platform. Allocation concealment will be ensured, as the allocation of patients is generated after the patient signs the informed consent form and thereby included in the study.

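### The tests named for outcome measures make no baseline adjustment for RAND36, although it is measured at baseline, so the quality-of-life comparison is less precise than it could be

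*Protocol article*

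**What the plan says.** Under Quality of life, the protocol article states: "Health-related quality of life is measured at baseline and at one and two years postoperatively using a Dutch translation of the RAND36 questionnaire". It lists nine domains and adds: "For each domain, a score of 0–100 is calculated". A baseline value on the same scale as the outcome is therefore already being collected.

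Under Data analysis, one general sentence covers the comparison of arms on all outcomes: "Groups will be compared using ANOVA-tests and χ^2^-tests (normal distribution) or Mann–Whitney *U*-tests (non-normal distribution) to analyze outcome measures". RAND36 is not named there, no covariate is named, and the analysed variable (follow-up score or change) is not given. Two other sentences in that section bear on baseline data. The first gives the scope of the model that includes the preoperative measurement: "repeated measure ANOVA will be used to analyze weight-loss patterns between the intervention groups and over time". The second reads: "Comparisons of baseline characteristics will be done descriptively".

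Patients are "randomized in a 2:1:1 ratio" by simple randomization, which gives 100 controls, 50 platform patients and 50 device patients.

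**The concern.** A preoperative score usually predicts part of the later score on the same questionnaire. A comparison that ignores it leaves that predictable part in the error term. A comparison of change scores uses the baseline but forces its coefficient to be 1, which adds noise when the correlation is low. Fitting the baseline as a covariate estimates the coefficient from the data and is at least as precise as either, apart from one degree of freedom.

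The named tests include no such adjustment, and the repeated measures model is reserved for weight loss. At stake is how well the trial can detect or exclude a quality-of-life difference with 50 patients in each eHealth arm. The sample size was set for BMI alone, so no precision was planned for RAND36.

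Leaving follow-up score versus change open also leaves two analyses available that can give different answers when the arms differ at baseline by chance.

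**Working it through.** **Inputs from the protocol article.** Arms of 100, 50 and 50 (Randomization and treatment allocation). Significance at 0.05, two-sided (Data analysis). For BMI, a difference of 4 with SD 8, "with power = 0.8 and α = 0.05" (Sample size calculation).

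**Assumptions.** The article gives no RAND36 effect, SD or baseline-to-follow-up correlation ρ. I take a standardized effect d = 0.5, the same ratio as for BMI (4/8), purely for illustration, and ρ = 0.3, 0.5 and 0.7. I also assume equal SDs at baseline and follow-up.

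**The plan's own figure.** For BMI, d = 4/8 = 0.5 with two controls per experimental patient gives 48 and 96; exact noncentral-t power is 0.802. Allowing 4% missing data, 48/0.96 = 50 and 96/0.96 = 100, hence 100 + 50 + 50 = 200. The stated sample size reproduces, and this point does not affect it.

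**Variance of the arm difference**, relative to follow-up scores alone (= 1):
- change score: 2(1 − ρ), which is 1.4, 1.0 and 0.6;
- baseline as covariate (ANCOVA): 1 − ρ², which is 0.91, 0.75 and 0.51.

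The ratio of change score to ANCOVA is 2(1 − ρ)/(1 − ρ²) = 2/(1 + ρ), which is 1.54, 1.33 and 1.18. It exceeds 1 for every ρ below 1. ANCOVA also beats follow-up scores alone whenever ρ is not 0.

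**Power, one eHealth arm versus control (50 versus 100).** Noncentrality = 0.5 / [√(1/50 + 1/100) × √(relative variance)], where √(1/50 + 1/100) = 0.173. For follow-up scores this is 0.5/0.173 = 2.89. For ANCOVA at ρ = 0.5 it is 2.89/√0.75 = 3.33. Two-sided α is 0.05.

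| Assumed ρ | Follow-up score | Change score | ANCOVA |
|---|---|---|---|
| 0.3 | 0.82 | 0.68 | 0.85 |
| 0.5 | 0.82 | 0.82 | 0.91 |
| 0.7 | 0.82 | 0.96 | 0.98 |

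At ρ = 0.5 both unadjusted readings give confidence intervals 1/√0.75 = 1.155 times as wide as the adjusted one. For device versus platform (50 versus 50) at ρ = 0.5, power is 0.70 under either unadjusted reading and 0.82 with ANCOVA.

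**Detectable difference.** Without any assumed effect, the difference detectable with 80% power at 50 versus 100 on follow-up scores is (1.96 + 0.84) × 0.173 = 0.485 SD. With ANCOVA it is 0.463, 0.420 and 0.347 SD at ρ = 0.3, 0.5 and 0.7.

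**The case against.** A reader might infer that the arms are compared only on follow-up scores and that the RAND36 baseline goes unused. The text does not support that. The sentence on tests is generic, and both ANOVA and Mann–Whitney can be run on changes from baseline. Elsewhere the article does think in terms of change: the study aim speaks of a reduction in BMI, and co-morbidity is classed as remission, improved or unimproved. On change scores at ρ = 0.7, the gain from ANCOVA is about 2 points of power (0.96 to 0.98), not the 16 that a comparison with follow-up scores would suggest (0.82 to 0.98).

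A reader might also count chance baseline imbalance under simple randomization as a second harm. It is the same loss. The ordinary standard error already includes it, and there is neither bias nor inflation of type I error.

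The strongest objection is that covariates for one secondary questionnaire are commonly left to an analysis plan, and this is a condensed article. That stands to the extent that a fuller document may already specify adjustment. It does not remove the point, because the article does more than stay silent: it names the tests for outcome measures and ties the one model with the preoperative value to weight loss.

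Finally, RAND36 is an unpowered secondary outcome. The abstract lists it first among the secondary outcomes, but the section on secondary outcomes begins with co-morbidity and no hierarchy is stated. That limits the severity.

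**Conclusion.** The point holds in a limited form and is minor. As published, the named tests make no baseline adjustment for RAND36 and leave open whether follow-up or change scores are compared. Whichever is meant, adjustment for the baseline score is at least as precise. At 50 versus 100, an assumed 0.5 SD effect and ρ = 0.5, the loss is about 9 points of power under either reading. At ρ = 0.3 it is about 3 points against follow-up scores and 17 against change scores; at ρ = 0.7 it is about 16 and 2. At ρ = 0 there is no gain over follow-up scores.

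These sizes rest on an effect borrowed from BMI, a correlation that the documents do not give, and equal SDs over time. The primary BMI analysis and the sample size are unaffected.

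**What to change.** Under Data analysis, add one sentence: each RAND36 level domain (the eight other than health change perception) is analysed at one and two years with a linear model on randomized group and the baseline score of the same domain, reporting adjusted mean differences with 95% confidence intervals. Leave health change perception unadjusted, because it already asks about change.

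The handling of skewed scores (robust or bootstrap standard errors, or a rank-based sensitivity analysis) can be left to the trial statistician.

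The cost is one sentence. No new data, visits or patients are needed, and the named SPSS package fits the model. The small downside is that patients without a baseline RAND36 score need a simple baseline imputation to stay in the analysis. The article reports that the trial is still recruiting, so the change can be made before any analysis.

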## Assessment of study outcomes

### Primary outcome measure

#### BMI

The primary outcome measure will be BMI. BMI is calculated with the formula: weight in kg / (height in m)^2^ = kg/m^2^. BMI is recorded through the whole follow-up scheme of five years which is standard care in this hospital. The weight of participants will be measured on calibrated electronic clinical weighing scales while fully clothed (without jackets or other items which can be removed quickly). For this study, BMI will be reported at one and two years postoperatively.

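### No planned analysis is tied to the two-year BMI difference versus control, and none uses preoperative BMI as a covariate; a baseline-adjusted two-year contrast costs nothing and is more precise

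*Protocol article*

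**What the plan says.** Study aim gives the primary hypothesis: adding eHealth "would lead to a larger reduction in body mass index (BMI) two years after the procedure compared to standard care".

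Sample size calculation uses the same target: "the addition of eHealth would reduce the BMI by another 4 point at two years postoperatively". The calculation is pairwise, for "independent control and experimental participants with two controls per experimental individual", and assumes that "the true difference in the experimental and control means changes is 4 BMI points with a standard deviation of 8".

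The primary outcome section adds a second time point: "For this study, BMI will be reported at one and two years postoperatively".

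Data analysis names two methods that could apply to BMI:

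- "Groups will be compared using ANOVA-tests" (or other tests, depending on the type and distribution of the variable), with no time point, pairwise contrast or covariate.
- "repeated measure ANOVA will be used to analyze weight-loss patterns between the intervention groups and over time". The levels of time are preoperative, one year and two years, so preoperative BMI is treated as an outcome.

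Neither is labelled as the primary analysis.

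**The concern.** The hypothesis and sample size rest on one quantity: each experimental arm's two-year BMI difference from control. The analysis section offers at least three tests: a one-way ANOVA at an unstated time, a repeated-measures group effect, and a group-by-time interaction. It does not say which one answers the hypothesis. They measure different things and can disagree, so the choice could be made after the results are seen.

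Preoperative BMI is also collected on every patient and is likely to correlate with two-year BMI, yet no analysis uses it as a covariate. That gives up precision that would cost nothing.

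**Working it through.** **Inputs from the article.** Difference 4, SD 8, 48 experimental and 96 control, two-sided alpha 0.05, power 0.80, 4% missing, total 200.

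**Inputs assumed, because the article gives none.** The correlation ρ between preoperative and two-year BMI, and the one-year difference d1 (0, 2 or 4 points).

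**1. The plan's own figure.** SE = 8·√(1/48 + 1/96) = 1.414. Noncentrality = 4/1.414 = 2.83 on 142 df, so power is 0.802. For missing data, 192/0.96 = 200. The stated sample size reproduces.

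**2. Repeated-measures group main effect.** This compares three-visit means. Randomized groups have no treatment effect before surgery, so the expected difference is (0 + d1 + 4)/3. With equal correlations and SD 8 at each visit, the SD of the mean is 8·√((1 + 2ρ)/3). Power for one experimental group versus control (48 versus 96):

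| d1 | Difference tested | ρ = 0.3 | ρ = 0.5 | ρ = 0.7 |
|---|---|---|---|---|
| 0 | 1.33 | 0.25 | 0.21 | 0.18 |
| 2 | 2.00 | 0.49 | 0.41 | 0.35 |
| 4 | 2.67 | 0.73 | 0.63 | 0.55 |

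The Discussion says that factors other than the procedure gain weight mainly after the first year, which points to the rows with smaller d1.

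**3. Group-by-time interaction.** With three groups and three visits it has (3 − 1)(3 − 1) = 4 df. Simulation of 96/48/48 (4,000 runs, Greenhouse-Geisser correction, SD 8; correlations 0.6 for baseline–1 y, 0.5 for baseline–2 y, 0.85 for 1 y–2 y):

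- Device effect 2 points at one year and 4 at two years, no platform effect: significant in about 0.72 of trials.
- The same effect in both experimental arms: about 0.85.
- Device effect 4 points at one year and **zero** at two years: significant in about 0.96 of trials.

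The last figure depends on the correlations. With equal correlations, an effect at one visit only gives the same interaction power whichever visit it is, so the figures for an effect at two years alone carry over: about 0.80 at ρ = 0.5 and 0.96 at ρ = 0.7.

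**4. ANOVA at two years.** As a three-group omnibus its power is about 0.76 if one experimental arm has the 4-point effect and about 0.88 if both do. It tests two-year BMI, but neither pairwise comparison with control.

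**5. Baseline-adjusted two-year contrast (ANCOVA), 48 versus 96.** The wording of the sample size leaves open whether SD 8 describes two-year BMI or change in BMI, so both are shown.

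*SD 8 is for two-year BMI:* residual SD = 8·√(1 − ρ²).

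| ρ | Residual SD | Unadjusted power | Adjusted power |
|---|---|---|---|
| 0.3 | 7.63 | 0.80 | 0.84 |
| 0.5 | 6.93 | 0.80 | 0.90 |
| 0.6 | 6.40 | 0.80 | 0.94 |

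*SD 8 is for change (equal SDs at both visits):* SD of BMI = 8/√(2(1 − ρ)), and the residual SD is that value times √(1 − ρ²).

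| ρ | SD of BMI | Residual SD | Unadjusted two-year power | Adjusted power |
|---|---|---|---|---|
| 0.3 | 6.76 | 6.45 | 0.91 | 0.94 |
| 0.5 | 8.00 | 6.93 | 0.80 | 0.90 |
| 0.6 | 8.94 | 7.16 | 0.71 | 0.88 |

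Under both readings the adjusted contrast is above the planned 0.80 throughout this range.

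**The case against.** A reader might infer that the planned analysis fails to test the two-year difference, that it ignores baseline BMI, and that the trial therefore lacks its stated power. The document does not support that, for four reasons.

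- **Repeated-measures ANOVA is not named as primary.** It is assigned to weight-loss patterns. With a two-year hypothesis, a natural reading is ANOVA on two-year BMI, with the repeated-measures model describing the curves. That ANOVA does test two-year BMI and is valid in a randomized comparison.
- **The interaction does use baseline.** It works on within-patient change, and its power can exceed 0.80: about 0.85 above with both arms active, and about 0.92 with one active arm and no one-year effect. The low main-effect figures matter only if that test were chosen.
- **The loss is relative to ANCOVA, not to the plan.** If SD 8 is for two-year BMI, the unadjusted pairwise comparison delivers the planned 0.80.
- **Covariates and model form are often left to an analysis plan**, which is not shown.

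The first three points stand and limit the finding. The fourth stands in part. The article does state its analyses, and as stated they leave open which test, at which visit and between which groups, answers the hypothesis.

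**Conclusion.** This is a free improvement, not an error in the sample size. The Data analysis section does not link any test to the two-year experimental-versus-control difference that the trial was sized for, and it uses preoperative BMI only as an outcome level.

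Two results need no assumed correlation, given a 4-point two-year effect. The group main effect is diluted to one third to two thirds of its size for a one-year effect between 0 and 4 points. The interaction is an omnibus test that responds to a one-year effect alone.

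The power figures do rest on assumptions: the correlations, an SD of 8 at each visit where simulated, and which arms have an effect. For ρ from 0.3 to 0.6, adjustment adds about 0.04 to 0.14 if SD 8 is for two-year BMI (0.84 − 0.80 to 0.94 − 0.80). If SD 8 is for change, it adds about 0.02 to 0.17 over an unadjusted two-year comparison (0.94 − 0.91 to 0.88 − 0.71).

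**What to change.** Before the data are analysed, state in the analysis plan:

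1. **Primary estimate:** the 24-month BMI difference of each experimental arm versus control, with 95% CI.
2. **Primary model:** ANCOVA of 24-month BMI on arm and preoperative BMI, or a mixed model of 12- and 24-month BMI with arm-by-visit terms and preoperative BMI as covariate. Adjustment for planned procedure is optional.
3. **Repeated-measures ANOVA:** kept as a description of weight-loss patterns, not as the test of the hypothesis.
4. **SD 8:** say whether it refers to two-year BMI or to change.

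The cost is wording only. The data, sample size and SPSS stay as planned.
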